### **3.13 Auditing**

This trial will be audited by independent reviewers for the participant enrolment, consent, eligibility, allocation to study groups and policies to protect participants, including reporting of AE and SAE based on regulation of each participating institutions.

## **4. Ethics and dissemination**

### **4.1 Research ethics approval**

The trial will be approved by the Institutional Review Board (IRB) at each of the participating institutions and will be conducted in accordance with GCP standards.

### **4.2 Protocol amendments**

Any modifications to the protocol which may impact on the conduct of the study, potential benefit of the patient or may affect patient safety, including changes of study objectives, study design, patient population, sample sizes, study procedures, or significant administrative aspects will require a formal amendment to the protocol. Such amendment will be agreed upon by the IRB prior to implementation, except in the case of changes made to protect patient safety, which will be implemented immediately.

### **4.3 Consent or assent**

Investigators or trained research nurses will introduce the trial to potential participants and their legal guardians regarding the main aspects of the trial. All participants and their legal guardians will receive adequate information about the nature, purpose, possible risks and benefits of the trial, and about alternative therapeutic choices, using an ICF approved by the IRB. The participants and their legal guardians will be given ample time and opportunity to ask questions and to consider participation in the trial. The ICF, signed by the participant and their legal guardians, is required for enrolment in the trial. The investigators will maintain the original and a copy of the signed consent form with the trial records.

### **4.4 Confidentiality**

All study related information will be stored securely at each study site. All participant information will be stored in locked file cabinets in areas with limited access.

To assure confidentiality, participants will be allocated a unique trial identification number throughout the trial. All records that contain names or other personal identifiers will be stored separately from study records identified by code number.

#### **4.5 Dissemination policy**

The protocol will be declared in a publicly accessible database (ClinicalTrials.gov). The trial will close out after the last participant's follow up data has been completed. The trial result will be disseminated through peer-reviewed publications and conference presentations.

### **Appendix B: Case Report Form**

### **Appendix C: Common Terminology Criteria for Adverse Events (CTCAE) version**

**4.03. (A complete copy of the CTCAE version 4.03 will be held in each site study file)**

## **Statistical analysis**

All of the baseline characteristics are used to study the comparability of both trial arms. The primary outcome evaluation and safety evaluation are carried out on the intention-to-treat (ITT) population. Continuous variables will be described using either the mean (standard deviation) or median (interquartile range), as appropriate, and categorical variables will use count (percentage). Participants' characteristics are compared using a  $\chi^2$  test for categorical variables and a t-test or Wilcoxon rank sum test for continuous variables.  $P$ -values < 0.05 are considered statistically significant.

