The risk of aspirin therapy in children with KD is considered to be low and appear to be similar to those reported in other settings. However, serious aspirin side effects have been reported in children treated for KD, including hepatic toxicity, gastritis, upper gastrointestinal bleeding, sensorineural hearing loss, and rarely, Reye’s syndrome.[19-22] Considering the risks of drug toxicity and the lack of evidence for preventing CAL formation, the role of high-dose aspirin in the acute phase of KD needs to be reassessed. Therefore, we initiate this multi-center, prospective, parallel-group, open-label, non-

inferiority RCT to investigate whether high-dose aspirin in the acute stage of KD has beneficial effects on the prevention of CAL formation.

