#### Secondary outcomes

- **IVIG resistance rate:**

IVIG resistance is defined as persistent or recrudescent fever at least 48 hours but not longer than 7 days after completion of the first IVIG treatment.

- **Duration of fever after IVIG treatment**

We will record the body temperature every 6 hour during the hospitalization period.

- **Duration of hospitalization**

We will record the hospitalization duration from admission (or arriving emergency room) to discharge date.

- **Laboratory data**

Laboratory data of CBC/DC, GOT/GPT, and CRP will be checked at baseline, day 5, and 6-8 week.

- **Z score of coronary arteries**

We will estimate Z score of the proximal segments of LMCA, LAD, and RCA at baseline, Day 5, 6-8 weeks, and 6 month with 2D echocardiography. The calculation of Z score is based on the website of Taiwan Society of Pediatric Cardiology ([http://www.tspc.org.tw/service/z\\_score.asp](http://www.tspc.org.tw/service/z_score.asp)).

- **CAL rate at 6 months**

- **Adverse event (AE) and serious adverse event (SAE)**

We will record AE and SAE. Severity of AE will be based on Common Terminology Criteria for Adverse Events (CTCAE) version 4.03.

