### **3.9 Blinding**

Participants and study investigators are unblinded to the group of IVIG alone or IVIG plus high-dose aspirin.

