### **3.11 Statistical methods**

All baseline characteristics will be used to investigate comparability of both trial arms. The primary outcome evaluation (CAL rate at 6-8 weeks) and secondary outcome of Z score of coronary arteries and CAL rate at 6 months will be performed on per-

protocol (PP) population while the other secondary outcome will be performed on intention-to-treat (ITT) population. Continuous variables will be described by using the mean (standard deviation) or median (interquartile range) as appropriate, categorical variables by using count (percentage). The participant characteristics will be compared using a  $\chi^2$  test for categorical variables, and a t test or Wilcoxon rank sum test for continuous variables. P values < 0.05 will be considered statistically significant.

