**Treatment Visit**  
**(Visit 3, Day 1)**

**IVIG treatment:**

start: 20□□/□□/□□/□□, end: 20□□/□□/□□/□□ (yyyy/mm/dd/hh)

**High-dose aspirin treatment** ☐None

start: 20□□/□□/□□/□□, end: 20□□/□□/□□/□□ (yyyy/mm/dd/hh)

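### Safety is analysed only by randomised arm; a supplementary table by high-dose aspirin actually received would guard against a modest, conditional dilution of the toxicity contrast

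*Combined protocol and SAP*

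**What the plan says.** The SAP text (Statistical analysis, after the appendices) states that the primary outcome and "safety evaluation are carried out on the intention-to-treat (ITT) population". Protocol section 3.11 reserves the per-protocol set for the primary outcome, coronary Z scores and CAL at 6 months, and then says that "the other secondary outcome will be performed on intention-to-treat (ITT) population". Section 3.4 lists AE, SAE and laboratory data (CBC/DC, GOT/GPT, CRP) among the secondary outcomes, so all of them fall to ITT. The two texts differ on the primary outcome, which is a separate matter; on safety they agree.

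ITT is expanded in the list of abbreviations but not defined. I read it in the usual sense, as all randomised children by assigned arm. No safety set, as-treated set or exposure-based sensitivity analysis appears in the text available for review.

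Three other places bear on the point:
- Section 2.1 gives aspirin toxicity as part of the reason for the trial: "Considering the risks of drug toxicity and the lack of evidence for preventing CAL formation".
- Section 3.9 makes the trial open-label: "Participants and study investigators are unblinded to the group of IVIG alone or IVIG plus high-dose aspirin".
- The CRF Treatment Visit page has a field "High-dose aspirin treatment" with a box for none and start and end times to the hour. The CRF adverse event page also records event start and end to the hour.

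**The concern.** An ITT safety table answers a fair question: what happens to children assigned to each strategy. It does not answer the question of what high-dose aspirin does to those who take it. Where the two diverge, ITT attributes an aspirin-related event in a test-arm child who received high-dose aspirin to IVIG alone, and keeps a standard-arm child who never took it in the aspirin denominator. Both errors bring the arms together, so harm from aspirin would tend to look smaller than it is.

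Departures are possible. Treatment is known to everyone, randomisation comes before treatment, the prohibited-treatment list in section 3.3 names steroids and biologic agents but not high-dose aspirin, and the CRF allows a free-text entry for treatment of IVIG resistance. SAEs are likely to be few, so one or two events counted under the wrong regimen could alter how the table reads. The data that would show this are already collected, but no planned analysis uses them.

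**Working it through.** **The plan's own figure.** The documents state no safety rate, safety power or crossover rate. Their only size figure is for efficacy (section 3.6), and it reproduces at one-sided alpha 0.05:

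n = (0.83 × 0.17 + 0.846 × 0.154) × (1.645 + 0.842)² / (0.10 + 0.016)² = 124.7, so 125 per arm; 125 / 0.9 = 138.9, so 139 per arm and 278 in total.

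This figure does not depend on the safety set. I use only the 139 per arm below.

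**Inputs for the dilution.**
- c_T, the share of the test arm that receives high-dose aspirin: 0 to 7.0%. The upper end is the IVIG-resistance rate in the retrospective group without high-dose aspirin (section 2.1): 38/546 = 7.0%. Using it as a ceiling supposes that every resistant child is given high-dose aspirin.
- c_S, the share of the standard arm that never starts it: 0 to 5%. This is an assumption; the documents give no figure.
- AE risk depends only on the regimen received (an assumption).

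**Formula.** Let p_A and p_0 be the AE risks with and without high-dose aspirin.

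Standard arm as randomised: p_A(1 − c_S) + p_0·c_S

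Test arm as randomised: p_0(1 − c_T) + p_A·c_T

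ITT difference = (p_A − p_0) × (1 − c_S − c_T)

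**Results.**

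| c_T | c_S | Share of contrast kept | True 10 points shows as |
|---|---|---|---|
| 0 | 0 | 100% | 10.0 |
| 0 | 5% | 95% | 9.5 |
| 7.0% | 0 | 93% | 9.3 |
| 7.0% | 5% | 88% | 8.8 |

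In children, the bottom row means about 0.07 × 139 = 9.7 in the test arm and 0.05 × 139 = 7.0 in the standard arm, so roughly 17 of 278.

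**Illustration of power**, with assumed AE risks of 15% with high-dose aspirin and 5% without, 139 per arm, two-sided 0.05. With no departures, power is 79.7%. In the bottom row:
- The arm risks become 0.15 × 0.95 + 0.05 × 0.05 = 14.5% and 0.05 × 0.93 + 0.15 × 0.07 = 5.7%, with mean 10.1%.
- The null standard error is √(0.101 × 0.899 × 2/139) = 0.0361.
- The alternative standard error is √((0.145 × 0.855 + 0.057 × 0.943)/139) = 0.0358.
- Power = Φ((0.088 − 1.96 × 0.0361)/0.0358) = Φ(0.48) = 68%.

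The risks of 15% and 5% are not from the documents; the example only shows scale.

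**The case against.** The strongest reply is that ITT safety is legitimate and keeps the randomised comparison, and that crossover here is conjecture. Both parts stand, and they limit the point to a missing supplementary analysis. Several stronger readings are tempting, and the documents do not support them.

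- A reader might infer that nothing keeps test-arm children from high-dose aspirin. Section 3.3 and the CRF Randomization Visit page assign IVIG without it, with emphasis, and the CRF field for treatment of resistance lists a second dose of IVIG and a free-text option, not aspirin. Crossover is possible, not described or expected.
- A reader might take 10% as the test-arm ceiling and reach a 15% shrinkage. The 31/305 = 10.2% belongs to the group that received high-dose aspirin; the proxy for the test regimen is 7.0%.
- A reader might count early stopping in the standard arm as misclassified exposure. Such a child was exposed and would stay in the same group. The regimen itself ends when fever subsides. Only children who never start would move.
- A reader might take toxicity as the whole rationale. Section 2.1 calls the risk low, pairs it with the lack of evidence for preventing CAL, and states the aim in terms of CAL prevention.
- A reader might conclude that an as-treated table should replace ITT. Switchers in this scenario would be persistently febrile and perhaps sicker. Moving whole children would carry their pre-aspirin events into the aspirin group. A longer stay would add observation time, because section 3.12 records AEs until discharge. That could overstate harm from aspirin.

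The 7.0% ceiling is also generous. Section 3.4 defines resistance by fever at least 48 hours after IVIG ends, so aspirin given for resistance would start late, and a late switcher need not carry the full aspirin-arm risk.

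**Conclusion.** The point holds as a cheap improvement, not as an error in the plan. Safety is analysed by assigned arm only, and any departure from the assigned aspirin regimen would bias the toxicity contrast toward zero. Under the stated assumptions the shrinkage is 0 to 12%, and it is zero if every child receives the assigned regimen. The range rests on a proxy for crossover, an unsourced 5% for non-receipt, and risk that follows the regimen received. It changes no number in the plan. The direction of the bias is more secure than its size.

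**What to change.** Keep the ITT safety table as planned and add to the SAP one supplementary table:

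- Population: all children who started study treatment.
- Grouping: high-dose aspirin actually received, from the CRF start and end fields.
- Timing: count an AE or SAE as aspirin-exposed only if its onset is at or after the first high-dose dose; earlier events count as unexposed. A switcher therefore contributes to both columns, and the denominators should say so.
- Laboratory data: group day 5 CBC and GOT/GPT by whether high-dose aspirin had begun before the sample.
- Report the number of children reclassified in each arm, so that the reader can see how much the ITT contrast could have been diluted.

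The cost is a short SAP paragraph and one table, with no new data collection and no change to sample size or endpoints. The drawback is that the exposure groups are not randomised for switchers, who may be sicker, so the table should be labelled as supportive of the ITT table.

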**Screen Visit**  
**(Visit 1, Day -3 to 0)**

**Visit Date:** 20□□/□□/□□ (yyyy/mm/dd)

**Admission (or emergency room) date:** 20□□/□□/□□ (yyyy/mm/dd)

**Fever start date:** 20□□/□□/□□/□□ (yyyy/mm/dd/hh)

**Demographic Data**

**Gender:** ☐ Male ☐ Female, **Birthday:** □□□□/□□/□□ (yyyy/mm/dd)

**Body weight:** □□.□ Kg, **Body height:** □□□.□ cm, **Body temperature:** □□.□ °C

**Baseline laboratory data date:** 20□□/□□/□□ (yyyy/mm/dd)

| Item | Value | Unit       | Item       | Value | Unit    | Item       | Value | Unit |
|------|-------|------------|------------|-------|---------|------------|-------|------|
| WBC  |       | 1000/ul    | MCHC       |       | gHb/dl  | Monocyte   |       | %    |
| RBC  |       | Million/ul | RDW-SD     |       | %       | Eosinophil |       | %    |
| HGB  |       | g/dl       | RDW-CV     |       | %       | Basophil   |       | %    |
| HCT  |       | %          | PLT        |       | 1000/ul | AST/GOT    |       | U/L  |
| MCV  |       | fL         | Segment    |       | %       | ALT/GPT    |       | U/L  |
| MCH  |       | pg/cell    | Lymphocyte |       | %       | CRP        |       | mg/L |

## Screen Visit (Visit 1, Day -3 to 0)

### Inclusion criteria:

- ☐Y ☐N 1. Male or female, age less than 6 years old
- ☐Y ☐N 2. Fulfilled the AHA criteria for KD as below:
- ☐ (1) Fever (more than 38.0°C ear temperature)  $\geq$  5 days, and 4 of the 5 following symptoms
  - ☐ (2) Diffuse mucosal inflammation (strawberry tongue, dry and fissured lips)
  - ☐ (3) Bilateral non-purulent conjunctivitis
  - ☐ (4) Dymorphous skin rashes
  - ☐ (5) Indurative edematous change over the hands and feet, or desquamation over the finger or toe tip
  - ☐ (6) Cervical lymphadenopathy (one or more nodule at least 1.5 cm in diameter)
- ☐Y ☐N 3. Informed consent form (ICF) signed by the patient or a legal guardian

### Exclusion criteria

- ☐Y ☐N 1. Symptoms not full fit the KD criteria
- ☐Y ☐N 2. Acute fever for  $\leq$  5 days or >10 days
- ☐Y ☐N 3. IVIG treatment at other hospital before refers to study site
- ☐Y ☐N 4. Treatment with corticosteroids, other than inhaled forms, in the previous 2 weeks
- ☐Y ☐N 5. Presence of a disease known to mimic Kawasaki disease (such as systemic juvenile idiopathic arthritis, Steven-Johnson Syndrome, Macrophage activation syndrome)
- ☐Y ☐N 6. Previous diagnosis of KD
- ☐Y ☐N 7. Inability to take aspirin (history of hypersensitivity to aspirin, G6PD deficiency, intolerance to aspirin)
- ☐Y ☐N 8. Inability to take IVIG (history of allergic reactions for IVIG, allergic reactions when testing dose of IVIG, selective IgA deficiency)
- ☐Y ☐N 9. Afebrile before enrolment
- ☐Y ☐N 10. Concomitant severe medical disorders (e.g. immunodeficiency, chromosomal anomalies, congenital heart diseases, metabolic diseases, nephritis, collagen diseases)
- ☐Y ☐N 11. Suspected severe infectious disease (e.g. sepsis, septic meningitis, peritonitis, bacterial pneumonia, varicella, and influenza)
- ☐Y ☐N 12. Conditions judged by the investigator as unsuitable for this trial

**Is the subject eligible to enter the trial?** ☐ YES ☐ NO

|                                                                                                                                                   |                                 |             |
|---------------------------------------------------------------------------------------------------------------------------------------------------|---------------------------------|-------------|
| I have reviewed all data recorded on all pages of this visit and certify that they are accurate, complete and consistent to the subject's record. | Investigator's Signature | Date |
|                                                                                                                                                   |                                 |             |

**Randomization Visit**  
**(Visit 2, Day 0 to 1)**

**Randomization number assignment date:** 20□□/□□/□□ (yyyy/mm/dd)

**Randomization number:** □□□

☐ **Test group:**

Patient will receive IVIG (2g/kg) in 10-12 hours alone, **without** high-dose aspirin. After fever subsides, low-dose aspirin (3-5mg/kg/day) will be prescribed until 6-8 weeks.

☐ **Standard group:**

Patient will receive IVIG (2g/kg) in 10-12 hours plus high-dose aspirin (80-100mg/kg/day, divided into four doses) till fever subside. After fever subsides, low-dose aspirin (3-5mg/kg/day) will be prescribed until 6-8 weeks.

|                                                                                                                                                   |                                 |             |
|---------------------------------------------------------------------------------------------------------------------------------------------------|---------------------------------|-------------|
| I have reviewed all data recorded on all pages of this visit and certify that they are accurate, complete and consistent to the subject's record. | Investigator's Signature | Date |
|                                                                                                                                                   |                                 |             |

**Treatment Visit**  
**(Visit 3, Day 1)**

**IVIG treatment:**

start: 20□□/□□/□□/□□, end: 20□□/□□/□□/□□ (yyyy/mm/dd/hh)

**High-dose aspirin treatment** ☐None

start: 20□□/□□/□□/□□, end: 20□□/□□/□□/□□ (yyyy/mm/dd/hh)

**Low-dose aspirin treatment**

start: 20□□/□□/□□/□□, end: 20□□/□□/□□/□□ (yyyy/mm/dd/hh)

**Body temperature (q4h)**

| Day 1 | °C | Day 2 | °C | Day 3 | °C | Day 4 | °C | Day 5 | °C |
|-------|----|-------|----|-------|----|-------|----|-------|----|
| :     |    | :     |    | :     |    | :     |    | :     |    |
| :     |    | :     |    | :     |    | :     |    | :     |    |
| :     |    | :     |    | :     |    | :     |    | :     |    |
| :     |    | :     |    | :     |    | :     |    | :     |    |
| :     |    | :     |    | :     |    | :     |    | :     |    |
| :     |    | :     |    | :     |    | :     |    | :     |    |

**Fever subside at:** 20□□/□□/□□/□□ (yyyy/mm/dd/hh)

**Antipyretic Drugs:** ☐Ibuprofen ☐Acetaminophen ☐Diclofenac

☐Others: \_\_\_\_\_

**IVIG resistance:** ☐YES ☐No

**Treatment for IVIG resistance:** ☐Second dose of IVIG

☐Others: \_\_\_\_\_

|                                                                                                                                                   |                                 |             |
|---------------------------------------------------------------------------------------------------------------------------------------------------|---------------------------------|-------------|
| I have reviewed all data recorded on all pages of this visit and certify that they are accurate, complete and consistent to the subject's record. | Investigator's Signature | Date |
|                                                                                                                                                   |                                 |             |

**Day 5 follow up Visit**  
**(Visit 4, Day 3 to 7)**

**Day 5 follow up laboratory data date:** 20□□/□□/□□ (yyyy/mm/dd)

| Item | Value | Unit       | Item       | Value | Unit    | Item       | Value | Unit |
|------|-------|------------|------------|-------|---------|------------|-------|------|
| WBC  |       | 1000/ul    | MCHC       |       | gHb/dl  | Monocyte   |       | %    |
| RBC  |       | Million/ul | RDW-SD     |       | %       | Eosinophil |       | %    |
| HGB  |       | g/dl       | RDW-CV     |       | %       | Basophil   |       | %    |
| HCT  |       | %          | PLT        |       | 1000/ul | AST/GOT    |       | U/L  |
| MCV  |       | fL         | Segment    |       | %       | ALT/GPT    |       | U/L  |
| MCH  |       | pg/cell    | Lymphocyte |       | %       | CRP        |       | mg/L |

**Day 5 follow up 2D echocardiography date:** 20□□/□□/□□ (yyyy/mm/dd)

Performer: \_\_\_\_\_

Body weight: □□.□ Kg

Body height: □□□.□ cm

LMCA: \_\_\_\_\_mm, Z score: \_\_\_\_\_

LAD: \_\_\_\_\_mm, Z score: \_\_\_\_\_

RCA: \_\_\_\_\_mm, Z score: \_\_\_\_\_

Coronary artery lesion: ☐Yes ☐No

Lesion type: \_\_\_\_\_

**Discharge date:** 20□□/□□/□□ (yyyy/mm/dd)

[figure not shown]

|                                                                                                                                                   |                                 |             |
|---------------------------------------------------------------------------------------------------------------------------------------------------|---------------------------------|-------------|
| I have reviewed all data recorded on all pages of this visit and certify that they are accurate, complete and consistent to the subject's record. | Investigator's Signature | Date |
|                                                                                                                                                   |                                 |             |

**Week 6-8 follow up Visit  
(Visit 5, Day 39 to 59)**

**Week 6-8 follow up laboratory data date:** 20□□/□□/□□ (yyyy/mm/dd)

| Item | Value | Unit       | Item       | Value | Unit    | Item       | Value | Unit |
|------|-------|------------|------------|-------|---------|------------|-------|------|
| WBC  |       | 1000/ul    | MCHC       |       | gHb/dl  | Monocyte   |       | %    |
| RBC  |       | Million/ul | RDW-SD     |       | %       | Eosinophil |       | %    |
| HGB  |       | g/dl       | RDW-CV     |       | %       | Basophil   |       | %    |
| HCT  |       | %          | PLT        |       | 1000/ul | AST/GOT    |       | U/L  |
| MCV  |       | fL         | Segment    |       | %       | ALT/GPT    |       | U/L  |
| MCH  |       | pg/cell    | Lymphocyte |       | %       | CRP        |       | mg/L |

**Week 6-8 follow up 2D echocardiography date:** 20□□/□□/□□ (yyyy/mm/dd)

Performer: \_\_\_\_\_

Body weight: □□.□ Kg

Body height: □□□.□ cm

LMCA: \_\_\_\_\_mm, Z score: \_\_\_\_\_

LAD: \_\_\_\_\_mm, Z score: \_\_\_\_\_

RCA: \_\_\_\_\_mm, Z score: \_\_\_\_\_

[figure not shown]

Coronary artery lesion: ☐Yes ☐No

Lesion type: \_\_\_\_\_

|                                                                                                                                                   |                                 |             |
|---------------------------------------------------------------------------------------------------------------------------------------------------|---------------------------------|-------------|
| I have reviewed all data recorded on all pages of this visit and certify that they are accurate, complete and consistent to the subject's record. | Investigator's Signature | Date |
|                                                                                                                                                   |                                 |             |

